### The reconfigurations

While there were numerous parallels between the London and Greater Manchester reconfigurations, there were also important differences.

Both reconfigurations were supported by local commissioners and received additional finance to support the changes. However, the London reconfiguration received significantly more resource per head of population: the London resource (£20 million) represented £2.42 per head of population (8.28 million
[14]), and £1,816.13 per estimated annual stroke admission, whereas the Greater Manchester resource (£3.5 million) represented £1.56 per head of population (2.24 million
[14]), and £1,174.81 per estimated annual stroke admission (Note estimates for stroke admission are derived from a peer-reviewed analysis of the South London Stroke Register
[15]).

Both reconfigurations went through similar processes, including consultation, data analysis, model development, and specification and selection of services. However, approaches to leadership and governance of these processes differed: the changes in Manchester were led by the Greater Manchester and Cheshire Cardiac and Stroke Network (which facilitates stakeholder collaboration to improve commissioning and provision of stroke and cardiac care across the Greater Manchester area), whereas in London they were led by Healthcare for London, a programme within the city’s Strategic Health Authority (the organisation responsible for managing all NHS commissioning and provider organisations within London). Therefore, the London reconfiguration was led by a body with greater executive authority. The proposed changes in London and Manchester both met with a degree of resistance, for example, from local communities, service providers, and public representatives. The ways in which this was managed by reconfiguration leaders had a significant influence on how the models developed.

In terms of the models applied, prior to reconfiguration, in both London and Greater Manchester, patients presenting with stroke were taken to the nearest accident and emergency (A&E) department to receive stroke care. Both of the reconfigurations aimed to concentrate specialist stroke services in ‘hub and spoke’ models of provision. However, there were significant differences in these models, in terms of the services provided by the different levels of the new systems and the criteria applied in deciding where patients should be treated in the two systems.

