#### Research questions

1. What were the key processes of and factors influencing the development and implementation of two reconfigurations of acute stroke services?

2. To what extent have changes delivered process and outcome improvements?

3. Have changes delivered improvements that stakeholders (e.g. commissioners, staff, patients and the public, and reconfiguration leads) think are worthwhile?

4. Have changes delivered value for money?

5. Has the additional investment in London provided better outcomes than those achieved for less resource in Manchester?

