## Design/methods

### Design

#### Understanding what works and at what cost

Identifying what process and outcome changes have occurred, and at what cost, provides evidence about the extent to which the reconfigurations have succeeded in their objectives of changing the system of service provision and quality of care. This component of the evaluation will analyse documentary evidence to establish the models applied in London and Greater Manchester; it will also identify whether any changes in process and outcomes can be associated with these changes.

In assessing the nature and results of the two reconfigurations, the evaluation will apply a controlled before-and-after design
[24]. This will compare the London and Manchester models in terms of the impact they had on processes, outcomes, and costs of care. In addition to comparing London with Greater Manchester pre- and post-reconfiguration, the analysis will make a wider comparison with the rest of England. This approach will permit observed changes to be analysed in the context of changes that take place in the rest of England over this period. A two-step approach will be taken to the analysis of outcomes: in the first instance, the impact of the reconfigurations on mortality and length of stay will be investigated; if evidence of impact on these is found, a more detailed cost-effectiveness analysis will be undertaken.

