### Analysis of outcomes

#### Econometric analysis

The outcome variables measured at the Trust level in each time period will be regressed against the covariates, with particular interest in interactions showing the impact of region following the introduction of stroke service reconfigurations. The regression model is:

$$y_{\mathrm{it}}=\alpha_{0}+\alpha_{1}A_{i}+\alpha_{2}Y_{t}+\alpha_{3}R_{\mathrm{it}}+\alpha_{4}X_{\mathrm{it}}+e_{\mathrm{it}}$$

where *y* is the outcome of interest (mortality, LOS), *i* indicates Trust, *t* indicates year, *A* is region, *Y* is year, *R* is an indicator variable taking the value one if stroke services in Trust *i* in each region *A* in year *t* have been reconfigured (1 = yes, 0 otherwise), *X* is a set of patient and Trust characteristics, the αs are coefficients to be estimated, and *e* is an error term. The regression model used will depend on the nature of the dependent variable. Of particular interest are the sign and statistical significance of the coefficient α_*3*_. If for reconfigurations in London or Greater Manchester α_*3*_ indicates a favourable result, i.e. a reduction in mortality and/or on LOS, the following cost-effectiveness analysis will be undertaken.

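### The econometric analysis reads its result from the sign and significance of α3 and defines no London-minus-Greater Manchester contrast, although the research questions ask for the size of effect and the difference between regions

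*Protocol article*

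**What the plan says.** In the protocol article, the Econometric analysis section regresses Trust-level outcomes on region, year, a reconfiguration indicator R and covariates. It states "Of particular interest are the sign and statistical significance of the coefficient" α3, the coefficient on R. The printed equation has one R and one α3. The text around it is regional: the section opens "with particular interest in interactions showing the impact of region following the introduction of stroke service reconfigurations", and the rule for going on to the cost-effectiveness analysis begins "If for reconfigurations in London or Greater Manchester". That rule is met if α3 "indicates a favourable result, i.e. a reduction in mortality and/or on LOS".

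The Research questions section sets two questions that this model has to serve. Question 2 is "To what extent have changes delivered process and outcome improvements". Question 5 is "Has the additional investment in London provided better outcomes than those achieved for less resource in Manchester". The Design section says of the controlled before-and-after design: "This will compare the London and Manchester models in terms of the impact they had on processes, outcomes, and costs of care". The sections on functional independence and on process changes apply the same regression model to their own measures.

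**The concern.** Question 2 is about the size of an effect and question 5 is about a difference between two effects. A p-value combines the size of the effect with the precision of its estimate, so it measures neither. If one region's coefficient is significant and the other's is not, that does not show that the two differ.

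This matters here because the regions are unequal in size. The Greater Manchester resource "represented £1.56 per head of population (2.24 million"), against 8.28 million people in London. With unequal precision, two equally effective reconfigurations can give different significance verdicts. A reader could then take London's larger investment to have bought better outcomes when the estimates do not show it. The article notes that other parts of the English NHS are looking to reconfigure stroke care, so this is the comparison others would act on.

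**Working it through.** **1. Reproduce the article's figures** (The reconfigurations).
- Resource per head: £20m / 8.28m = £2.42; £3.5m / 2.24m = £1.56. Both agree with the text.
- Implied admissions a year: 20,000,000 / 1,816.13 = 11,012 in London; 3,500,000 / 1,174.81 = 2,979 in Greater Manchester.
- Ratio: 2,979 / 11,012 = 0.27, the same as the population ratio 2.24 / 8.28.

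**2. Relative precision.** The article gives no variance, effect size or power, so two assumptions are compared.
- (a) Precision follows patient numbers: SE ratio = √(11,012 / 2,979) = √3.70 = 1.92.
- (b) Precision follows the number of units. Greater Manchester has 10 Trusts. London's Trust count is not given, so its 24 Stroke Units serve as a proxy: SE ratio = √(24 / 10) = 1.55.

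**3. Chance of unlike verdicts when the true effects are equal.** Also assumed: two-sided 5% tests, independent regional estimates and a large rest-of-England comparator.
- Let z = 1.96 + the normal quantile of London's power.
- Greater Manchester power = Φ(z / SE ratio − 1.96).
- P(London significant, Greater Manchester not) = London power × (1 − Greater Manchester power).

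Worked case at 80% London power under (a): z = 1.96 + 0.84 = 2.80; 2.80 / 1.92 − 1.96 ≈ −0.50; Φ ≈ 0.31; 0.80 × (1 − 0.31) ≈ 0.55.

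| London power | GM power (a) | London only (a) | Both (a) | GM power (b) | London only (b) | Both (b) |
|---|---|---|---|---|---|---|
| 50% | 17% | 41% | 9% | 24% | 38% | 12% |
| 80% | 31% | 55% | 25% | 44% | 45% | 35% |
| 90% | 39% | 55% | 35% | 55% | 40% | 50% |
| 95% | 47% | 51% | 44% | 64% | 34% | 61% |
| 99% | 61% | 39% | 60% | 79% | 21% | 78% |

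Under (a) the London-only result peaks at 56% and exceeds 50% only for London power of about 65–95%. Under (b) it peaks at 45%.

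**4. By size of effect.** Assume baseline mortality of 12–25%, five years before and 3.5 years after, and patient-level variance only. The London-only probability is then 35–50% for a 0.5-point fall and 31–52% for a 1-point fall. For a 2-point fall it is at most about 4%, because both regions are then well powered.

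**5. The alternative.** A test of the London-minus-Greater Manchester contrast calls two equal effects different 5% of the time, whatever the SE ratio. Its own precision is limited: with independent estimates under (a), its SE is √(1 + 3.70) = 2.17 times London's.

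**6. What the printed model can supply.** With one R term, α3 is a single effect shared by the reconfigured Trusts of both regions. It yields neither regional effects nor a contrast. If the model is instead fitted once per region, as the wording of the cost-effectiveness rule suggests, it yields two coefficients and two verdicts, but still no stated contrast.

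**The case against.** The strongest reply is that no misreading is planned. Naming sign and significance as of particular interest is an emphasis, not a reporting rule. The Design section, the opening of the Econometric analysis section and the section on process changes all signal a comparison between regions. The only explicit decision rule is a reduction in either region, with no significance threshold in that sentence. The cost-effectiveness model is then populated for both regions and uses mean differences with probabilistic sensitivity analysis. Reporting confidence intervals is a detail that an article may leave to a fuller plan.

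Much of this stands. A reader might infer that a non-significant Greater Manchester coefficient will be reported as no impact, or will drop Greater Manchester from the economic analysis. The article states neither, and its rule for proceeding points against the second. A reader might also infer that equal reconfigurations would most likely be reported as a London success and a Greater Manchester failure. The documents do not support that. The SE ratio of 1.92 assumes that precision follows patient numbers, whereas outcomes are modelled at Trust level, the before and after periods differ, and Greater Manchester was phased in. The London-only result exceeds 50% only within a band of London power, never does so on the 10 v 24 proxy, and nothing in the article places the study in that band.

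The reply does not meet the central point. The article does fix an inferential criterion, and it does not fit questions 2 and 5. The intended comparison has no defined quantity, and the printed equation cannot produce one.

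**Conclusion.** The point holds as a mismatch between the stated criterion and the research questions, together with an undefined regional contrast. Greater Manchester has about 0.27 of London's estimated admissions, so its estimate is likely to be the less precise. With equal true effects, a significant London result beside a non-significant Greater Manchester one has a probability of about 55% at 80–90% London power and 39% at 99%, if precision follows patient numbers. On the Trust proxy the figure peaks at about 45%, and for large effects it is small under either assumption. These figures rest on the assumptions listed above, since the article gives no power or effect size. They show that equal reconfigurations could readily look different, not that they will. The change is worth making because the stated criterion bears on the study's main comparative question and a sound alternative is cheap.

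**What to change.** Write the model with separate reconfiguration indicators for London and Greater Manchester in one joint fit. This makes explicit the regional interaction that the text already alludes to. Replace the sentence on sign and significance with wording such as: *The result for each region is its estimated effect with a 95% confidence interval. Any claim that one reconfiguration did better than the other rests on the 95% confidence interval for the London-minus-Greater Manchester contrast from the same model. A non-significant regional effect is reported as the range of effects not excluded.* Apply the same to the analyses of functional independence and of process changes.

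The cost is one extra model term and no new data. This is more than a wording change, because the contrast does not exist until the terms are separated. The drawback is that the Greater Manchester effect, or the contrast, may have to be called inconclusive.

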#### Analysis of process changes

To analyse process changes, the regression model described for the econometric analysis of impact on outcomes will be applied to process variables, covering the same ‘before’ and ‘after’ periods. This will allow an assessment of whether relative performance across London and Greater Manchester remains constant pre- and post-reconfiguration – i.e. whether the reconfigurations are associated with changes in processes of care. Extending the ‘location’ comparison to include the rest of the English NHS will permit these changes to be assessed in the context of any nationwide changes that may have taken place over the period analysed.

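### The printed regression has one reconfiguration coefficient and no region-by-reconfiguration term, contradicting its own text and leaving no parameter for the London versus Greater Manchester comparison

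*Protocol article*

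**What the plan says.** The Econometric analysis section introduces the model "with particular interest in interactions showing the impact of region following the introduction of stroke service reconfigurations". It then prints y_it = α0 + α1·A_i + α2·Y_t + α3·R_it + α4·X_it + e_it, where A is region, Y is year and X is a set of patient and Trust characteristics. R "is an indicator variable taking the value one if stroke services in Trust" i has been reconfigured by year t, and zero otherwise. The inferential rule is: "Of particular interest are the sign and statistical significance of the coefficient" α3. The step to cost-effectiveness begins "If for reconfigurations in London or Greater Manchester" α3 is favourable, meaning lower mortality or shorter stay.

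Three other places need the two regions' effects kept apart:
- Research questions, question 5: "Has the additional investment in London provided better outcomes than those achieved for less resource in Manchester"?
- Design, Understanding what works and at what cost: "This will compare the London and Manchester models in terms of the impact they had on processes, outcomes, and costs of care".
- Analysis of process changes: "the regression model described for the econometric analysis of impact on outcomes will be applied to process variables", so as to judge "whether relative performance across London and Greater Manchester remains constant pre- and post-reconfiguration".

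Analysis of functional independence reuses the same regression.

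**The concern.** The text expects one effect for each region, and the equation supplies one effect in total. Region enters only through α1·A_i, which moves a region's level in all years alike and says nothing about how that region changed on reconfiguration.

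A common effect is hard to defend here because the article describes two different interventions. In London every suspected stroke goes to a hyperacute unit. In Greater Manchester only patients presenting within four hours go to a comprehensive or primary centre, and the rest go to the nearest district centre, much as before. An analyst who follows the equation would report a single number for mortality and length of stay, and again for function and process. That number could not differ by region, so the regression would be silent on the comparison that the design section sets as its aim.

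**Working it through.** The article gives no sample size, power or effect figure for this analysis, so there is no figure to reproduce. The check is algebraic, followed by a noise-free illustration.

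**Algebra.** Hold year and X fixed. In the printed model, E[y | R=1] − E[y | R=0] = α3 for every Trust, whatever A_i is. The term α1·A_i is the same before and after, so it cancels. The modelled London effect minus the modelled Greater Manchester effect is α3 − α3 = 0. This step needs no assumption about Trust numbers, dates or effect sizes.

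**What α3 estimates when the true effects differ.** Let them be δL (London) and δM (Greater Manchester). Least squares with region and year terms gives α3 = wL·δL + wM·δM, with wL + wM = 1.

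From the document:
- data run from 2004 to 2013;
- the London model was implemented in 2010;
- Greater Manchester is served by 10 hospital organisations;
- data stop when services begin to change and resume when the new model is fully in place.

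Assumed, because the document does not give them:
- the number of London Trusts (the article counts 8 hyperacute units and 24 stroke units, not Trusts);
- 110 Trusts in the rest of England;
- London before 2004–09 and after 2011–13; Greater Manchester before 2004–08 and after 2010–13;
- equal Trust weights.

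| Trusts: London / Greater Manchester / rest | wL | wM |
|---|---|---|
| 24 / 10 / 110 | 0.678 | 0.322 |
| 30 / 10 / 110 | 0.723 | 0.277 |
| 8 / 10 / 110 | 0.417 | 0.583 |

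Example, first row: with δL = −1.5 points and δM = 0, α3 = 0.678 × (−1.5) + 0.322 × 0 = −1.02 points, reported for both regions.

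**Second set of dates.** No years are omitted, London starts in 2010, Greater Manchester starts in 2009, 2010 or 2011, and there are 24, 30 or 32 London Trusts. When both regions start in 2010 the weights are simply the Trust shares, for example 24/34 = 0.706. Results over all nine combinations:
- true effects −2 (London) and 0 (Greater Manchester): α3 from −1.38 to −1.56;
- 0 and −2: α3 from −0.44 to −0.62;
- −2 and +2: α3 from −0.77 to −1.13, favourable although Greater Manchester worsened.

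**After the change.** With R×London and R×Greater Manchester in place of R, the fit returned both true effects exactly in each of these nine combinations, and the design matrix had full rank in every layout above. The contrast needed for question 5 can therefore be estimated from the data already planned.

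**The case against.** The strongest reply is that the equation is shorthand. It also writes one α1 for region, one α2 for year and one α4 for a whole set of covariates, and any analyst would expand those into several coefficients. If α3 is expanded in the same way, R becomes a pair of regional indicators, as the sentence on interactions and the London-or-Greater-Manchester wording suggest. This stands as evidence of intent. A reader might infer that the investigators chose to assume equal effects, and the surrounding text does not support that. It does not rescue the equation, because R is explicitly defined as one 0/1 variable and neither an expanded R nor separate regional fits are written.

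A second reply is that an article may leave the exact contrast to the full analysis plan. On its own, a missing contrast would be no finding. The point here is that the model as stated conflicts with the text beside it.

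A third reply concerns consequences, and it largely stands. The cost-effectiveness model is populated for London and Greater Manchester separately, before and after. It is tempting to say that pooling sends a region with no effect on to cost-effectiveness analysis, or credits it there with the other region's benefit. The document does not support this: the trigger is worded as either region, the analysis that follows covers both, and each region enters with its own data. It is equally tempting to object that comparing two separate significance results would mislead, but the article never proposes that comparison for question 5.

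**Conclusion.** The equation in Econometric analysis contradicts its own text. Fitted as printed, it gives both regions one averaged effect and has no parameter for the London versus Greater Manchester difference sought by question 5, the design section and the process analysis. That conclusion rests on the definition of R alone.

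The size of the averaging rests on assumptions. The London weight is about 0.68 with 24/10/110 Trusts and runs from 0.42 to 0.72 across the assumed London counts in the table. These figures show that averaging occurs and can hide opposite effects; they do not measure a bias in this study.

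A reader might go further and conclude that question 5 cannot be answered anywhere in the study. That is too strong. The region-specific cost-effectiveness model addresses it in part, although that model is run only if α3 is favourable and does not supply a regression contrast for mortality, length of stay, function or process.

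**What to change.** In Econometric analysis, replace α3·R_it with α3L·R_it·London_i + α3M·R_it·GM_i, so that each region's effect is estimated against the rest of England. Then:
- apply the section's decision rule to α3L and α3M separately;
- name α3L − α3M, with its confidence interval, as the regression's answer to question 5;
- use the same form in Analysis of functional independence and Analysis of process changes.

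This adds one term and one linear contrast and needs no new data. The cost is precision: each regional interval will be wider than the interval for the single pooled coefficient.

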#### Objectives

1. To identify the barriers and facilitators for major system reconfiguration, implementation, and sustainability.

2. To study whether the reconfigurations have delivered clinical and cost effective improvements that patients and public think are worthwhile.

3. To identify lessons about major service reconfiguration that might be applied in other settings (i.e. other locations and other service domains).

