#### Analysis of process and outcome data

Routinely collected data will be analysed for two purposes. First, to analyse outcomes, econometric and cost effectiveness analyses will be conducted. Second, there will be an analysis of whether the reconfigurations are associated with significant changes in how services were provided, i.e. an analysis of process measures.

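### The cost-effectiveness analysis is run only after a favourable mortality or length-of-stay result, although the value-for-money question it must answer carries no condition

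*Protocol article*

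**What the plan says.** The condition appears twice in the protocol article.

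- Under Design, in the section on what works and at what cost, mortality and length of stay (LOS) are examined first, and "if evidence of impact on these is found, a more detailed cost-effectiveness analysis will be undertaken".
- Under Econometric analysis the trigger is a favourable coefficient α3 in either region. The sentence begins "If for reconfigurations in London or Greater Manchester" and ends "i.e. a reduction in mortality and/or on LOS, the following cost-effectiveness analysis will be undertaken". The sentence before it reads "Of particular interest are the sign and statistical significance of the coefficient".

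The commitments that this analysis serves carry no condition.

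- Research question 4: "Have changes delivered value for money".
- Objective 2: "To study whether the reconfigurations have delivered clinical and cost effective improvements".
- Analysis of process and outcome data: "econometric and cost effectiveness analyses will be conducted".

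The section on cost-effectiveness describes a discrete event simulation model that has already been developed. It is to be populated for both London and Greater Manchester, before and after implementation, with deterministic and probabilistic sensitivity analysis.

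**The concern.** Value for money depends on costs and effects together. Extra spending that buys no detectable benefit is an answer to research question 4. So is an imprecise benefit, because the uncertainty about cost-effectiveness can be quantified and reported. Under the rule as written, the study would be silent in exactly these cases, and an economic result would appear only after a favourable effect had been seen. A commissioner considering a similar reconfiguration would then have no cost-effectiveness evidence from a null or unfavourable result.

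The rule also cannot be applied unambiguously. The text does not say whether a favourable sign is enough or whether significance is required, and that choice largely decides whether the analysis takes place.

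**Working it through.** **Reading the passages together.** The Design section requires evidence of impact, with no direction given. The Econometric analysis section requires a reduction. An increase in mortality would therefore satisfy the Design section and fail the Econometric analysis section. Neither section provides an economic analysis for a null or imprecise α3. The documentary analysis contributes information on the cost of change, but it does not set that cost against outcomes, so it cannot answer research question 4.

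**Money at stake** (section The reconfigurations): £20 million / 8.28 million = £2.42 per head in London; £3.5 million / 2.24 million = £1.56 per head in Greater Manchester. Both agree with the stated figures.

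**How often the gate opens with no true effect.** The article gives no significance level, number of tests or power, so these inputs are assumptions:

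- *Number of tests, k.* The regression section names mortality and LOS, which over two regions gives k = 4. If all three mortality measures under Data collection count (in hospital, 30 days, one year), then k = (3 + 1) × 2 = 8.
- *Level.* Two-sided 5%, so 2.5% in the favourable direction.
- *Regions.* Independent of each other. Outcomes within a region are independent or positively correlated.

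With independent tests, the chance of at least one favourable result is 1 − 0.5^k on sign and 1 − 0.975^k on significance.

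| Tests | Within-region correlation | Sign alone | Significance |
|---|---|---|---|
| 4 | 0 | 1 − 0.5^4 = 93.8% | 1 − 0.975^4 = 9.6% |
| 4 | 0.9 | 81.7% | 6.9% |
| 8 | 0 | 1 − 0.5^8 = 99.6% | 1 − 0.975^8 = 18.3% |
| 8 | 0.8 (simulated) | 90% | 11% |

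For 4 tests at correlation 0.9, the chance that both outcomes in a region miss the threshold is 0.4282 on sign and 0.9648 on significance. So 1 − 0.4282² = 81.7% and 1 − 0.9648² = 6.9%.

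**How often the gate stays closed although a benefit is real** (significance reading). For one outcome this is 1 − power: 80%, 50% and 20% at power 0.2, 0.5 and 0.8. For two independent outcomes of equal power it is (1 − power)²: 64%, 25% and 4%.

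**Selection of favourable estimates.** Let θ be the true effect in standard errors: 2.80, 1.96 and 1.12 at power 0.8, 0.5 and 0.2. The expected exaggeration of a single estimate that must pass threshold c is E[Z | Z > c] / θ.

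| Power | Its own significance (c = 1.96) | Its own sign (c = 0) |
|---|---|---|
| 0.8 | 1.12 | 1.00 |
| 0.5 | 1.41 | 1.03 |
| 0.2 | 2.25 | 1.22 |

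These factors apply to an estimate gated on itself. The gate here opens if any one of several results is favourable, which dilutes the effect. In a simulation of an any-of-8 significance gate with equal true effects and within-region correlation 0.8, the factors fall to about 1.00, 1.06 and 1.34 at the same powers.

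**The case against.** The best defence is that a two-step design saves effort: if nothing improved, a detailed economic model may seem unnecessary. That has some force on resources. It does not remove the conflict with an unconditional research question, and the saving is small because the model already exists.

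A second defence is that an article may leave such detail to a fuller document. That does not apply, because the article states the rule; it is not silent on it.

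Several stronger readings are tempting, and the article does not support them.

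- *A region without a favourable result gets no cost-effectiveness ratio, so London and Manchester are never compared.* The trigger is London or Greater Manchester, and the model is then populated for both. One favourable region brings in the other. Research question 5, "Has the additional investment in London provided better outcomes than those achieved for less resource in Manchester", also concerns outcomes, which the ungated regional analysis partly addresses. The economic comparison is lost only when neither region passes.
- *Opening the gate on LOS alone rewards harm, because early death shortens stay.* Opening it only starts an analysis that uses 90-day deaths and QALYs, where harm could show. Mortality is also analysed in its own right.
- *Functional gain drives the QALYs yet cannot open the gate.* It is true that function is not a trigger. The article does not describe how QALYs arise in the model, and function is analysed without any condition where data are available.
- *The published ratio will be inflated by a known factor.* The size depends on unstated power and on the reading of the gate. The model is described as populated with before-and-after data, not with α3, so any carry-over comes only through shared data sources.

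**Conclusion.** The point stands as a defective rule. If neither region shows a favourable result, research question 4 and the cost-effectiveness part of objective 2 have no economic answer, contrary to the article's own statement that the analysis will be done. This follows from the text and needs no numerical assumption.

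The ambiguity of the trigger is material: about 82–99.6% against about 7–18% with no true effect. Those ranges rest on the assumed 4 to 8 tests, a two-sided 5% level, independent regions and within-region correlations from 0 to 0.8 or 0.9. On the sign reading the analysis would seldom be blocked by a true null; on the significance reading it usually would be. The article does not say which applies.

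Selection is a secondary concern of unknown size and should not be presented as a predicted bias in the ratio. The change should be made, but the point does not undermine the regression analysis or the rest of the evaluation.

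**What to change.** Delete the condition in the Design section and in Econometric analysis, so that both agree with the research questions, objective 2 and the section on process and outcome data. Run the simulation model for London and for Greater Manchester whatever the sign or significance of α3.

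For each region, and for the comparison between them, report incremental costs, incremental outcomes, the ICER or net monetary benefit, and the probability of cost-effectiveness from the probabilistic sensitivity analysis already planned. Net monetary benefit is the safer summary where the difference in deaths or QALYs is near zero, because the ratio is then unstable.

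With the gate gone, there is no need to define its trigger, and no selection arises from it. The cost is some analyst time that the gate might have saved.
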